### 2.1. Study Design

The pilot study will follow a parallel group cluster randomized controlled trial. Randomization will be carried out at the cluster level to minimize the risk of contamination, and clusters will be defined as distinct units within LTCF residencies (i.e., separate floors or buildings, not sharing common areas or group activities, with minimal social interactions between clusters). A 6-month multicomponent intervention will be delivered and compared with usual care. Participants assigned to the multicomponent intervention will receive a 6-month program including Mediterranean diet and functional foods, physical exercise, and cognitive stimulation (see Multidomain intervention section). Participants in the intervention group will also be offered vaccinations according to the national vaccination calendar. The study protocol will include baseline evaluations (T0), a 6-month multidomain intervention, and follow-up assessments at 3 months (T1), 6 months (T2), and 9 months (T3). Participants in the control group will continue the standard care provided in their respective LTCFs, including their usual physical and cognitive stimulation activities, as well as their usual diet. Participants assigned to the control group will receive general information on healthy lifestyle and health, including risk factors. Figure 1 shows the flow diagram of the I-COUNT study protocol.

This protocol was designed in accordance with the CONSORT guidelines for feasibility and pilot studies. See the online Supplementary Materials for the CONSORT checklist figure. Participants or the public were not involved in the design of the study protocol.

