#### 2.2.1. Sample Size

The endpoint related to sample size refers to changes in gut microbiota composition between the two groups (multidomain intervention; control) assessed at 3-month follow-up compared to baseline. As suggested by Sim and Lewis to maximize precision and efficacy for pilot studies [29], a sample size of 30 individuals in the intervention group and 30 individuals in the control group is planned for each participating LTCF. This resulted in a total of 60 participants per group (120 in total). This allows for the detection of an effect size of 0.52 with 80% power and alpha = 0.05, considering a simplified approach assuming a two-sample *t*-test with equal variance (PASS 2024, version 24.0.1).

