#### 2.2.2. Randomization and Blinding

Two LTCFs will participate in the I-COUNT study, and within each LTCF, two units (floors or flats) will be randomly assigned to either the intervention or control group using the SAS Plan procedure. Participants will not be informed of their group allocation until the completion of the baseline assessment. Outcome evaluators will be blinded to participants’ group assignments, and participants will be instructed not to disclose this information to the assessors. The geriatricians and neuropsychologists responsible for developing the training activities will be different from the outcome assessors. If maintaining blinding for the outcome assessors is not feasible, additional assessors will be recruited to ensure impartiality.

Data will be processed in accordance with the European Regulation on the use of personal data (679/2016) and Legislative Decree no. 196 ss.ii. 30 June 2003, as amended by Legislative Decree no. 101 of 10 August 2018, as well as Deliberation of the Privacy Guarantor no. 52 of 24 July 2008 and subsequent updates.

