#### 2.7.3. Statistical Analyses

Descriptive statistics will be calculated in relation to feasibility measures (recruitment and retention rates over the study period, adherence metrics, technological acceptability, completeness of data collected and operational challenges).

Continuous variables will be compared between groups through mixed models, with random effects at the cluster level and treatment group as fixed effects. The potential health impact of multidomain interventions will be estimated considering changes over time for continuous variables analyzed through mixed models for repeated measures, with group and time, and group x time interaction as fixed effects, and cluster and patients as random effects.

The continuous variables considered in comparison between groups for fecal microbiota analyses will include measures of species richness (α-diversity), the relative abundance of specific bacterial taxa, and the representation of genes involved in key bacterial metabolic pathways. The effects of the intervention on the overall fecal microbiome composition will also be assessed comparing intervention and control groups on different time points with Bray–Curtis dissimilarity on principal coordinate analysis.

Data available for participants with complete data will be considered, but also an intention-to-treat (ITT) approach with imputation for missing data will be applied.

Results with a *p*-value < 0.05 will be considered statistically significant. Analyses will be performed using SAS software version 9.4 (SAS Institute, Cary, NC, USA).

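### Neither planned mixed model adjusts for the baseline value, and omitting facility inflates the standard error of single-visit group comparisons only

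*Protocol article*

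**What the plan says.** Section 2.7.3 specifies the models term by term. Continuous variables are compared between groups by mixed models "with random effects at the cluster level and treatment group as fixed effects". Health impact, as change over time, is estimated by "mixed models for repeated measures, with group and time, and group x time interaction as fixed effects, and cluster and patients as random effects". No baseline covariate and no facility term appears in either list.

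On the design, section 2.1 states: "Randomization will be carried out at the cluster level to minimize the risk of contamination". Section 2.2.2 adds that "within each LTCF, two units (floors or flats) will be randomly assigned to either the intervention or control group using the SAS Plan procedure", and section 2.2.1 that "a sample size of 30 individuals in the intervention group and 30 individuals in the control group is planned for each participating LTCF". Together these give two facilities with one unit per arm in each: four units of 30 residents.

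Section 2.2.1 sets the sample-size endpoint as the microbiota change from baseline to 3 months. Section 2.3.4 provides for a stool sample at T0. Section 2.5 makes stool the only T1 assessment; the other outcomes return at T2 and T3. The Discussion says that the pilot's effect sizes and variability estimates will feed the sample size of the definitive trial.

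**The concern.** With four randomised units, the arms can easily differ at baseline by chance. T0 is measured for the primary outcome and for most continuous secondary outcomes, so the information to deal with this is already planned, but the stated models either ignore it or use it only by subtraction.

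Facility raises a second, smaller issue. Two units in the same arm always lie in different facilities. A cluster variance estimated without a facility term therefore contains the difference between facilities, although that difference cancels from the treatment contrast. This affects the standard error of a comparison at one visit. It also affects the cluster variance that would be carried into the planning of the next trial.

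**Working it through.** **The plan's own figure.** Section 2.2.1 says "This allows for the detection of an effect size of 0.52 with 80% power and alpha = 0.05", "considering a simplified approach assuming a two-sample" t-test. The normal approximation gives (1.960 + 0.842) × √(2/60) = 0.511. The exact t-test with 118 degrees of freedom (df) gives 0.516, and 80.6% power at 0.52. The figure reproduces. It involves neither baseline nor facility, so it does not settle this point.

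**Assumptions (not in the article).** Total SD is 1. r is the baseline to follow-up correlation of a resident within a unit. s_f, s_u and s_e are the variance shares of facility, unit within facility, and resident.

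**Chance baseline imbalance.** The arm difference has variance s_u + s_e/30.
- All of a between-unit share of 0.05 at unit level: √(0.05 + 0.95/30) = 0.286. The chance of a difference beyond 0.3 SD is 2·P(Z > 0.3/0.286) = 29%.
- Half of it due to facility: √(0.025 + 0.95/30) = 0.238, and 2·P(Z > 0.3/0.238) = 21%.

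**How much imbalance reaches the estimate** (s_f = 0.05, s_u = 0.05, s_e = 0.90, r = 0.6).
- Follow-up only: (s_u + r·s_e/30)/(s_u + s_e/30) = (0.05 + 0.018)/(0.05 + 0.03) = 0.85.
- Change score: 0.85 − 1 = −0.15.
- With an added unit-by-time share of 0.01 to 0.02, simulation gives 0.76 to 0.68 and −0.24 to −0.32.

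**Resident-level precision.** Variances are proportional to 1 (follow-up only), 2(1 − r) (change) and 1 − r² (adjusted). The ratios are therefore (1 + r)/2 against change and 1 − r² against follow-up only.

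| r | against change | against follow-up only |
|---|---|---|
| 0.3 | 0.65 | 0.91 |
| 0.5 | 0.75 | 0.75 |
| 0.7 | 0.85 | 0.51 |

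**Whole contrast.** These ratios cover the resident part only. Add stable unit differences, with r = 0.5 and s_e/30 = 0.95/30 = 0.0317. The formulas are:
- follow-up only: s_u + s_e/30
- change: 2(1 − r)·s_e/30
- covariate with the within-unit slope r: (1 − r)²·s_u + (1 − r²)·s_e/30
- constrained baseline, variances known: (s_u + s_e/30)(1 − b²), with b = (s_u + r·s_e/30)/(s_u + s_e/30), which is 0.721 at s_u = 0.025 and 0.806 at s_u = 0.05

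| s_u | follow-up only | change | covariate | constrained baseline |
|---|---|---|---|---|
| 0.025 | 0.0567 | 0.0317 | 0.0300 | 0.0272 |
| 0.05 | 0.0817 | 0.0317 | 0.0363 | 0.0286 |

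The gain over follow-up only is large. The gain over the change score is modest (0.0272/0.0317 = 0.86; 0.0286/0.0317 = 0.90). A plain covariate can lose slightly to the change score when unit differences are large and fully stable.

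**Facility, single visit.** The true variance is s_u + s_e/30. Without a facility term the model targets s_f + s_u + s_e/30.
- With s_f = s_u = 0.025 the SE is 0.286 instead of 0.238.
- With s_u from 0.01 to 0.05, the SE is too large by a factor of 1.12–1.21 (s_f = 0.02), 1.27–1.49 (0.05) or 1.51–1.88 (0.10).
- On 2 df the simulated type I error falls from 0.050 to 0.034 (s_f = 0.05) or 0.027 (s_f = 0.10), which is conservative.

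**Facility, group-by-time.** The facility main effect cancels. At s_f = 0.05 the simulated and model SEs are both 0.155, and rejection is 0.048 with or without a facility effect.

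**Variance for planning.** Under the half split the pooled cluster term targets an ICC of 0.05, and the within-facility ICC is 0.025/0.975 = 0.026. With 30 residents per unit the design effects are 1 + 29 × 0.05 = 2.45 and 1 + 29 × 0.0256 = 1.74.

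**Cost of a facility fixed effect.** Four unit means less two arms leave 2 df; a facility term leaves 1. The 95% half-width goes from 4.30 × 0.286 = 1.23 to 12.71 × 0.238 = 3.02.

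**The case against.** The strongest reply is that the repeated-measures model, which the article assigns to health impact, already handles most of this. A reader might infer that its error bars are wrong because facility is missing, or that chance unit imbalance stays in its estimate. The documents do not support either. With T0 as a time level, subtraction removes the facility main effect and most of the baseline difference, and the contrast is unbiased on average. What remains there is efficiency and some regression to the mean.

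Three further limits stand.
- Section 2.7.3 does not say that the group-only model is applied to follow-up values, nor that T0 is in the response vector. Both are readings, the second the more natural one.
- A reader might assume that T0 exists for every outcome. Sections 2.3 to 2.3.4 describe no T0 measurement of falls, hospital admissions, mNTB or waist circumference.
- A facility fixed effect is not free: it lowers the SE but widens the interval about 2.5 times (3.02/1.23), and section 2.7.3 keeps a 0.05 significance threshold.

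It may also be said that an analysis plan could add covariates, and that a pilot does not claim definitive efficacy. The first carries limited weight, because the article lists the fixed and random effects explicitly instead of deferring them. The second lowers the stakes but does not remove them, since the estimates are meant for planning.

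**Conclusion.** The point holds in limited form. The stated models make no baseline adjustment. A group-only comparison at follow-up would carry about 0.7 to 0.85 of any baseline difference between arms. The change-score contrast would carry about −0.15 to −0.3 and is less precise at resident level, by a factor of 1/0.75 = 1.33 in variance at r = 0.5. Across the whole contrast the advantage over the change score is smaller and depends on how stable the unit differences are, which favours the constrained-baseline form.

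Omitting facility makes single-visit standard errors too large and mixes facility variance into the cluster variance. It leaves the group-by-time contrast unaffected. Four units estimate any of these variances poorly, whichever model is used.

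The ICC, its facility share, the unit-by-time share and r are all assumptions. The directions follow from the design; the sizes do not.

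**What to change.** In section 2.7.3, state the role of T0. For the continuous microbiota measures and every other continuous outcome with a T0 measurement, use one of two forms:
- T0 as a covariate, with the later visits as responses (T1, T2 and T3 for microbiota; T2 and T3 otherwise); or
- a constrained-baseline model with a common T0 mean in both arms.

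Report the group difference at each visit from that model. This changes wording only and uses data already planned. Outcomes without a T0 measurement need their own statement.

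Facility can be added for point estimates and variance components. Because a fixed facility effect leaves 1 between-unit df, the same edit should say that between-group results are descriptive and are not tested at 0.05. The cost is giving up those tests.

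The edit should also state the df method and whether a unit-by-time term is included. With an unmodelled unit-by-time share of 0.01 or 0.02, the group-by-time test rejected in 14.5% or 22.8% of simulated null trials. Baseline adjustment and a facility term do not address that.

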### 2.7. Analytical Approach

#### 2.7.1. Outcomes

The feasibility of the multidomain intervention will be assessed by considering the acceptability and the participants’ adherence to the interventions. In particular, feasibility outcomes will include the following:Recruitment and retention rates over the study period;Adherence metrics (attendance at training sessions, completion of cognitive modules, dietary compliance);Technological acceptability, assessed via user feedback and actual usage data (wearable sensors, digital apps);Completeness and quality of data collected across domains;Operational challenges, including staffing, logistics, and data management within LTCFs.

The primary health outcome of this short-term pilot study is the evaluation of changes in gut microbiota composition and the differences between the two groups (multidomain intervention and control groups) at the 3-month follow-up point (T1). The gut microbiota has emerged as a central player in the gut–brain–muscle axis, and growing evidence suggests it may influence metabolism, inflammation, muscle function, and neurocognitive processes, making it a valuable biomarker in multidomain interventions for older adults [54].

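### The random effects listed for the change model cancel out of the group-by-time contrast, so its error bars are too small if unit-level change over time varies at all

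*Protocol article*

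**What the plan says.** Section 2.1 makes the unit the thing randomised: "Randomization will be carried out at the cluster level to minimize the risk of contamination". Section 2.2.2 says that within each of the two facilities "two units (floors or flats) will be randomly assigned to either the intervention or control group". Section 2.2.1 adds that "a sample size of 30 individuals in the intervention group and 30 individuals in the control group is planned for each participating LTCF". Together these give four clusters, two per arm, of about 30 residents each.

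Section 2.7.3 describes two mixed models. The first compares continuous variables between groups, with treatment as a fixed effect and a random effect at cluster level. The second estimates the potential health impact through changes over time, "with group and time, and group x time interaction as fixed effects, and cluster and patients as random effects". No cluster-by-time term, cluster slope or cluster-level test is listed for it. Results with p below 0.05 are to be called significant.

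The primary health outcome in 2.7.1 concerns "changes in gut microbiota composition and the differences between the two groups" at T1. The Discussion says that the pilot's effect sizes and variability estimates will be used to size the definitive trial.

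**The concern.** The second model looks as if it allows for clustering, because cluster appears among its random effects. A cluster effect without a time index protects comparisons of level at one visit. It does nothing for a comparison of change, because the same quantity is present at T0 and at follow-up and is subtracted away.

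What remains unmodelled is change shared by the residents of one unit. Section 2.1 defines units so that they do not share common areas or group activities, and exercise and cognitive sessions are run in groups of 3 to 5. Anything that shifts on one floor between visits (meals, staffing, an outbreak) would be counted as treatment effect, with a standard error that assumes independent residents.

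Two things are at stake: the interval and p-value for the effect on change, and the variability passed to the definitive trial, which would lack the unit-level component of change that a cluster trial needs.

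**Working it through.** **Inputs.** Four units, 30 residents per unit, 60 per arm (2.2.1, 2.2.2); visits T0 to T3 (2.1); two-sided 5% test (the side is assumed, and it reproduces the plan's figure). The ICC of change is not given, so 0 to 0.10 is an assumed range.

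**The plan's own figure.** Section 2.2.1 claims "detection of an effect size of 0.52 with 80% power and alpha = 0.05" for a two-sample t-test. With 60 per group and 118 degrees of freedom, the detectable effect is 0.516, and power at 0.52 is 80.6%. The figure reproduces, but it treats residents as independent.

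**Cancellation.** Write the model as y = group + time + group×time + u(cluster) + b(patient) + e. For one resident, y(T1) − y(T0) contains neither u nor b. With patient and residual variances of 0.5 each (illustrative), the variance of one resident's change is 2 × 0.5 = 1, so the standard error of group×T1 is √(2 × 1/60) = 0.1826. A generalised least squares calculation gave the same values with two and with four visits:

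| Cluster-intercept variance | SE, group difference at T0 | SE, group×T1 |
|---|---|---|
| 0 | 0.183 | 0.1826 |
| 0.1 | 0.365 | 0.1826 |
| 0.5 | 0.730 | 0.1826 |
| 2 | 1.426 | 0.1826 |

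The cluster intercept moves the comparison of levels and leaves the comparison of change untouched.

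**Adding unit-level change.** Take a cluster-by-time variance of 0.025. Each unit's change gains variance 2 × 0.025 = 0.05, which is an ICC of change of 0.05/1.05 = 0.048. With two units per arm, the contrast gains 0.05/2 + 0.05/2 = 0.05. Its true standard error is √(0.0333 + 0.05) = 0.289, against 0.183 without that term.

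**False-positive rate, single contrast.** The design effect is 1 + 29ρ, where ρ is the ICC of change. The true standard error is √(1 + 29ρ) times the one computed as if residents were independent. The approximate rejection rate is 2[1 − Φ(1.96/√(1 + 29ρ))]. The simulation used 20,000 null trials per setting.

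| Assumed ρ | Design effect | SE ratio | Approximate rate | Simulated rate | t-test on four unit means |
|---|---|---|---|---|---|
| 0 | 1.00 | 1.00 | 0.050 | 0.049 | 0.050 |
| 0.01 | 1.29 | 1.14 | 0.084 | 0.085 | 0.049 |
| 0.05 | 2.45 | 1.57 | 0.210 | 0.212 | 0.050 |
| 0.10 | 3.90 | 1.97 | 0.321 | 0.336 | 0.050 |

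**Overall test over four visits.** With time as a category this test has 3 numerator degrees of freedom. At ρ = 0.05 the scaled chi-square approximation, P(χ²₃ > 7.81/2.45), gives about 36%, and simulation gives about 37% to 38%. Under section 2.5 only the stool samples are planned at all four visits, so this larger figure concerns the microbiota measures.

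**The case against.** **The wording may allow more than intercepts.** The text says random effects, not intercepts, and it is one sentence in a journal article without its analysis plan. That is a fair caution about certainty. But the article does list the random effects, and no term that varies with time is among them. Time-constant effects are the plain reading. An unstructured covariance for the patient's residuals would not help, because the missing component is shared between residents.

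**The other model carries clustering.** This stands. The between-group model in 2.7.3 has a cluster effect, and the microbiota paragraph speaks of comparison between groups. A reader might infer that the whole analysis, or the primary microbiota comparison as such, ignores the randomised unit. The documents do not support that: they leave open which model carries the primary comparison at T1, and only the test of change in the second model has this fault.

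**The harm is conditional.** This also stands. If unit-level change does not vary, the test is correct (simulated rate 0.049). Every inflation figure rests on an assumed ICC.

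**It is a pilot.** The Discussion disclaims definitive testing of efficacy, which limits the consequence. The 0.05 threshold and the reuse of variability estimates remain.

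**Few clusters are a separate problem.** A small-sample correction applied to the listed model would not cure this fault, since that model has no variance component for unit-level change to which a correction could attach.

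**Conclusion.** The point holds, conditionally. On the plain reading of 2.7.3, the group-by-time test ignores the unit of randomisation, and its error bars are too small for any non-zero unit-by-time variance. Cancellation is exact for complete balanced data; with missed visits a little between-unit information re-enters. For a single contrast the false-positive rate is about 9%, 21% and 33% at an assumed ICC of change of 0.01, 0.05 and 0.10, and about 5% at zero. The overall four-visit test reaches about 38% at 0.05.

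The documents do not show that the trial's intervals will in fact be wrong by a given amount, because they state no ICC. The between-group model is outside this finding. The study's exploratory purpose makes this something that should be corrected before analysis, not a fault that undermines the pilot.

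**What to change.** In 2.7.3, state that the interval and p-value for the effect on change come from the four unit-mean changes from T0, using a t-test with 2 degrees of freedom. This test held about 5% at every ICC tried. It does not use the allocation of units within each facility.

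Alternatively, list random effects for cluster, cluster-by-time and patient, and fix the degrees of freedom for group-by-time at the cluster level. The two options are not equivalent. With four units the cluster-by-time variance is estimated as zero in about 53% of trials at an ICC of 0.01 and 32% at 0.05. If the degrees of freedom are not fixed, those fits fall back to the resident-level test.

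Report the effect on change as exploratory, and give any cluster-by-time variance with its wide uncertainty when it is passed on for planning.

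The cost is one sentence and, for the alternative, one model term; no new data are needed. Statistically, intervals widen and power is low. With 2 degrees of freedom, the effect detectable at 80% power is about 1.03, 1.17, 1.62 and 2.04 SD at an ICC of 0, 0.01, 0.05 and 0.10, against the stated 0.52. Power at 0.52 is about 36%, 30%, 19% and 14%.

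### The primary health outcome is powered as one variable but analysed as several families of microbiota variables under a flat p < 0.05 rule, so its false-positive risk exceeds the stated 5%

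*Protocol article*

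**What the plan says.** Section 2.7.1 (Outcomes) states: "The primary health outcome of this short-term pilot study is the evaluation of changes in gut microbiota composition and the differences between the two groups", assessed at T1. It names no index, taxon or distance. Microbiota at T2 and T3 is listed among the secondary outcomes.

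Section 2.2.1 (Sample Size) ties the power statement to the same quantity: "The endpoint related to sample size refers to changes in gut microbiota composition between the two groups". With 60 residents per group it gives a detectable effect size of 0.52 at 80% power and alpha 0.05, from an equal-variance two-sample t-test that the article itself calls simplified.

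Section 2.7.3 (Statistical Analyses) lists the continuous variables to be compared between groups: "measures of species richness (α-diversity), the relative abundance of specific bacterial taxa, and the representation of genes" in metabolic pathways. Overall composition is assessed separately, by "comparing intervention and control groups on different time points with Bray–Curtis dissimilarity on principal coordinate analysis". The section closes with a single rule for p-values: a "value < 0.05 will be considered statistically significant". It sets no order among these variables.

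**The concern.** A two-sample t-test at alpha 0.05 describes one comparison on one number per resident. The analysis section offers at least three families of such numbers, each in the plural, and any of them could be reported as the primary health outcome. The article does not say which one the 0.52 belongs to. A p-value under 0.05 on any of them would satisfy the stated rule, so the error rate for the outcome as a whole is not the 5% in the sample-size statement.

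The next trial is also affected. The Discussion says that effect sizes and variability from this pilot will feed its sample-size calculation. An effect picked because it crossed 0.05 among several candidates is biased upward, and a trial sized on it would be too small.

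**Working it through.** **Inputs.** From section 2.2.1: 60 per group, d = 0.52, power 80%, alpha 0.05 (sidedness not stated). From section 2.7.3: three families of continuous variables plus an ordination, and a threshold of 0.05. The number of variables tested, k, is not in the article, so a range is shown.

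**1. The plan's own figure.** Two-sided normal approximation: d = (1.960 + 0.842) × √(2/60) = 2.802 × 0.1826 = 0.51. The exact t-test gives 0.516, and power at d = 0.52 is 80.6%. The 0.52 is therefore reproduced for one test at two-sided 0.05. A one-sided test would give 0.457.

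**2. Chance of at least one false positive.** Assume no true effect on any variable and that each test holds its nominal 0.05. For independent tests the chance is 1 − 0.95^k. For equally correlated normal tests with correlation ρ it is 1 − ∫ φ(u) [Φ((c − √ρ·u)/√(1−ρ)) − Φ((−c − √ρ·u)/√(1−ρ))]^k du, with c = 1.96. The values of ρ are assumptions.

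| k | independent | ρ = 0.3 | ρ = 0.5 | ρ = 0.8 |
|---|---|---|---|---|
| 1 | 5.0% | 5.0% | 5.0% | 5.0% |
| 3 | 14.3% | – | – | – |
| 4 | 18.5% | 17.4% | 15.6% | 11.4% |
| 20 | 64.2% | 54.0% | 41.9% | 22.4% |
| 50 | 92.3% | 80.5% | 62.2% | 29.9% |
| 100 | 99.4% | 94.3% | 77.7% | 35.9% |

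(– means not calculated.) The row k = 3 is one test per family. The row k = 4 allows one more, for example a test attached to the overall-composition analysis.

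**3. Tests needed for a near-certain false positive.** For 90%: k = ln(0.10)/ln(0.95) = 44.9, so 45. For 95%: k = ln(0.05)/ln(0.95) = 58.4, so 59. Both assume independence. At ρ = 0.5, even 200 tests give only 90.3%.

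**4. What a full adjustment would do to the power statement.** Bonferroni with 60 per group:

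| k | alpha per test | power at d = 0.52 | detectable d at 80% power |
|---|---|---|---|
| 1 | 0.05 | 80.6% | 0.52 |
| 4 | 0.0125 | 62.3% | 0.62 |
| 20 | 0.0025 | 40.9% | 0.72 |

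The stated 5% error and 80% power at d = 0.52 hold together only if one variable is primary.

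**5. Selection and the next trial.** Under the same simplified t-test (118 degrees of freedom, critical value 1.98), a result passes 0.05 only if the observed standardized difference is at least 1.98 × √(2/60) = 0.36. A variable with no true effect that is selected for passing would therefore carry an apparent effect of 0.36 or more into the later calculation.

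**The case against.** The strongest reply has four parts.

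- **The study is a pilot.** Feasibility is its main objective, and the article calls its health findings exploratory and not a definitive test of efficacy. This softens the consequence. It does not remove it, because the pilot's effect sizes are to be used for the next trial, and a flat significance rule sits badly with exploratory status.
- **An article condenses.** The list of taxa, the handling of zeros, any transformation and a false discovery rate procedure may all be in an analysis plan that is not shown. That is fair, and none of it is counted as missing here. But the article itself states a primary health outcome, a power calculation, families of variables and a threshold, and these do not fit together.
- **The 0.52 is generic.** The group size follows a recommendation for pilot studies, and the 0.52 only reports what that size can detect. A standardized effect can apply to any single continuous variable. True, but it still needs one.
- **Microbiota features are correlated.** They come from the same stool sample, so the independent-test figures are upper values. This stands, and the table shows the reduction.

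Three stronger readings are tempting but unsupported. A reader might infer that a false-positive primary result is close to certain. That needs some 45 to 59 independent tests, whereas the article gives no count and speaks only of specific taxa and key pathways. A reader might also infer that the ordination is judged at p < 0.05, but "Bray–Curtis dissimilarity on principal coordinate analysis" yields no p-value by itself, and no test is named. Finally, a reader might infer that relative abundances enter the models untransformed. The article is silent on this, which is not the same as saying so.

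**Conclusion.** The concern holds in a limited form. The primary health outcome is sized as one continuous variable and analysed as several, with one threshold and no lead variable, so the 5% in the sample-size statement is not held for it. The excess runs from about 14% to 19% with 3 to 4 independent tests, through 64% with 20, to over 90% with 45 or more. With 20 tests it is about 42% at an assumed correlation of 0.5.

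These figures assume that k takes the values shown, that the 0.05 rule is applied to unadjusted p-values (the article does not say otherwise), and that each single test holds its nominal level. Clustering is a separate matter and is not included. Because the study is a declared pilot, this is a point that should be corrected rather than one that invalidates the design.

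**What to change.** - **Section 2.7.1:** name one scalar microbiota variable, measured as change from T0 to T1, as the primary health outcome. An α-diversity measure is one workable choice. If overall composition is what is meant, name one Bray–Curtis-based test as the primary analysis instead.
- **Section 2.2.1:** say that the 0.52, 80% power and alpha 0.05 refer to that variable. If a distance-based test is chosen, the t-test statement does not describe it and needs its own justification.
- **Section 2.7.3:** limit the 0.05 rule to the named primary variable. Declare all other richness measures, taxa, pathways and time points exploratory, with Benjamini–Hochberg false discovery rate control, and keep the ordination as a descriptive display.

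The cost is wording in three sections and minor programming, with no change to recruitment or sampling. The downside is that individual taxa and pathways can no longer be called significant at raw 0.05.
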